### Study design

This study is a concurrent mixed methods realist evaluation, consisting of two methods of data collection: 1) a quantitative before and after survey, and 2) qualitative interviews with trainees. Both methods of data collection will sample VCSE service providers and pharmacy students evenly, for comparison. The quantitative survey will be used to generate data on the extent and distribution of outcomes and how these differ between VCSE service providers and pharmacy students (context) [35], whilst the realist interviews will help to explain how and why these outcomes are produced, by linking them to CMO configurations. The quantitative survey was designed to be complimentary to existing evaluations of HCS training, to also aid comparison between groups of trainees [25,28,31]. A between-subjects design for the quantitative survey will aid comparison between participant groups. Ethical approval has been obtained from Northumbria University prior to recruitment and data collection (Project ID: 10429).

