### Quantitative pre- and post- survey

The quantitative before and after survey will be administered pre (immediately before receipt of training), post (immediately following training) and follow-up (8–10 weeks after training) to both participant groups. Opportunity sampling will be employed, such that all eligible trainees within the study period (August 2025 to April 2026) will be invited to complete the surveys. Where possible, the trainer ([name]) or coordinator of the training (e.g., a key contact at the University) will send the pre survey to trainees around 1 week before training. A QR code to complete the pre survey will also be displayed on the first slide of the training, with time provided at the start of the training for trainees to complete it. At the end of the training, a QR code to complete the post-survey will be provided and all trainees will be asked to complete it. Trainees will be encouraged to complete the post survey before leaving the training site, or at least within the next 24 hours following training (although will be able to access the link at any time). Eight weeks after the training, the trainer or coordinator of the training will send trainees a link to complete the follow-up survey. Since training to VCSE service providers is often as part of mixed professional groups and to avoid isolation of VCSE service providers, all attendees of mixed groups containing VCSE service providers will be invited to complete the surveys. Using Gpower to calculate the total sample size required to detect a significant difference in confidence, perceived usefulness, perceived importance, and competence between trainee groups, to detect a small effect size (0.3) at 80% power, a minimum total sample size of 352 (176 in each group) is required to detect a significant difference in confidence and competence post training between participant groups (two groups t test (correlations not available to calculate for multiple linear regression), two tailed, p < .05). With an added 10% margin to account for missing data (that is not missing at random), the target sample size is 387 (194 per group). If the target sample size is not reached, the available data will be analysed acknowledging that the analyses was underpowered as a limitation. As secondary analyses, differences pre and post within each group will also be tested.

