Quantitative data will be analysed using SPSS [46]. To create a mean score for competency of ODQs and SMARTER goal facilitation, responses to the four scenarios for each skill will be aggregately coded by two independent coders (BN and another author), using established coding matrices adapted from previous studies [28]. Any discrepancies will be resolved through discussion with a third independent reviewer ([name]). Thus, aggregate scores (mean score across the four scenarios) will be calculated for both skills. Recall of the HCS philosophy will also be scored by two independent coders (BN and another author) and resolved through discussion with a third reviewer ([name]), using a self-created rubric available in the OSF pre-registration: https://osf.io/wpbn3/files. The data from attendees who are not undergraduate pharmacy students or service providers from the VCSE will not be included in the inferential analyses but will be summarised descriptively. Descriptive statistics will be produced for demographic characteristics, and pre and post scores relating to confidence, perceived usefulness, perceived importance, and competence (for both VCSE service providers and undergraduate pharmacy students). Exploratory baseline differences between professional groups for confidence, perceived usefulness, perceived importance, and competence will be tested through independent samples t-tests (or Mann-Whitney U tests if assumptions for an independent samples test are not met, tested using the Shapiro-Wilk test and Levene’s test for homogeneity of variances). Exploratory differences between trainee groups in post HCS ‘lite’ training (post survey) responses for perceived usefulness, perceived importance, and competence will be tested using a multiple logistic regression, controlling for baseline values (pre survey), age, and gender. Changes in confidence, perceived usefulness, perceived importance, and competence pre and post HCS ‘lite’ training will be tested within groups (conducted for both VCSE service providers and undergraduate pharmacy students) through within-subjects t-tests (or Wilcoxon Signed Rank tests If normality assumptions are not met, tested using the using Shapiro-Wilk test). Statistical testing will aid comparison with the existing literature of how HCS impact the confidence and competence of trainees across different settings. For the current realist evaluation, statistical testing will look to test (refine, support, refute) the IPTs, and therefore analysis will look to ‘preserve’ the configurations in analysis. For example, comparison across participant groups (undergraduate pharmacy students and VCSE service providers) will be tested for a relationship with proposed outcomes (motivation, competence, and confidence). If quantitative variables do not meet normality assumptions, non-parametric tests will be applied.

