## Discussion

This realist evaluation will produce a refined programme theory which explains how and why a specific approach to MECC training, HCS, works, including how it works differently for different audiences and thus how it might need to be adapted to ensure that all trainees are equipped equally to deliver MECC conversations. By including both undergraduate pharmacy students and VCSE service providers, this study will enable comparison based on a number of potentially important contextual factors. VCSE service providers do not work in a healthcare setting and may not have a healthcare background or any prior knowledge of health promotion, so may not view MECC as relevant to them [30]. However, they often have highly diverse specialist backgrounds and are experienced and confident in talking to service users, strongly driven by a desire for social good [30]. Meanwhile, undergraduate pharmacy students are trained as healthcare professionals, including to deliver healthy lifestyle advice, with health promotion now considered a key part of a Pharmacist’s role [55]. However, undergraduate pharmacy students may have had little experience of interacting with service users and have chosen to study pharmacy for a range of reasons [56]. The realist evaluation allows for these contextual differences to be incorporated into the analysis, to provide further understanding about what elements of HCS work for whom and why. The findings will be published in a peer reviewed journal, submitted prior to April 2027. Additionally, the findings will be disseminated with key stakeholders (including the stakeholder involvement group for this study), providing recommendations to optimise impact of the evaluation.

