Nevertheless, the key target outcome of the current realist evaluation is to inform approaches to MECC training across the UK and beyond. Ensuring that MECC training is effective in helping people to deliver MECC conversations may help to create a culture around health promotion and prevention. There is currently no specific guidance about how MECC training is delivered, indicating the potential for policy-level impact of the current study. For example, if HCS is demonstrated to increase confidence and competence no matter the background of trainees, there is rationale for MECC policy to specify HCS training as the approach to MECC delivery. Alternatively, both approaches may instead complement each other, providing a rationale to include elements of both. MECC is also unique in that it raises the possibility of health promotion outside of healthcare settings, opening new opportunities to prevent disease. Due to trusting relationships within the VCSE, there is rationale that MECC within the VCSE may be more impactful than when delivered in other settings (e.g., healthcare) where the service provider is not known to the service user. Assessing whether HCS ‘lite’ training is sufficient to enable service providers from the VCSE to deliver MECC is the first step to evaluating the impact of MECC within the VCSE. Also, by utilising existing measures to assess the change in confidence, motivation, and competence following HCS ‘lite’ training, the results of the survey will contribute to the existing literature supporting HCS ‘lite’ training, and aid comparison between other trainee groups (e.g., staff at Sure Start children’s centres, physiotherapists) [23,31]. Thus, the current study will provide a holistic understanding of what elements of HCS training work for whom, under what circumstances, in what respects, to what extent, and why, and in the process informing the same questions about MECC training overall.

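### Separate pre/post tests compared in narrative cannot show whether the two groups gain differently or alike, and the between-group regression leaves out confidence

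*Protocol article*

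**What the plan says.** All places are in the protocol article.

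- **Quantitative pre- and post- survey, sample size.** The study is sized for a difference between groups: "to detect a small effect size (0.3) at 80% power, a minimum total sample size of 352 (176 in each group) is required" (two-group t test, "two tailed, p < .05"). The outcomes named for this comparison include confidence and competence. On a shortfall: "If the target sample size is not reached, the available data will be analysed acknowledging that the analyses was underpowered as a limitation".
- **Same section, analysis.** Baseline differences between groups are tested for all four outcomes. Post-training differences are tested in a regression adjusted for baseline, age and gender. Its outcomes are usefulness, importance and competence; confidence is not listed. Then: "Changes in confidence, perceived usefulness, perceived importance, and competence pre and post HCS ‘lite’ training will be tested within groups". A later general sentence mentions relating participant group to motivation, competence and confidence, but names no method.
- **Discussion, anticipated challenges.** Reaching the target sample is called the main challenge. With a smaller sample, the within-group tests would still be run and their results compared between groups in narrative form.
- **Discussion, policy.** The example of policy impact begins "if HCS is demonstrated to increase confidence and competence no matter the background of trainees".
- **Study design.** "Both methods of data collection will sample VCSE service providers and pharmacy students evenly, for comparison".

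**The concern.** The survey's purpose is to show how outcomes differ between VCSE service providers and pharmacy students. Running one test in each group and setting the two results side by side does not estimate that difference. Two significant results can hide a large gap. One significant and one non-significant result can arise from equal gains, particularly when group sizes differ. A non-significant group difference does not show similarity either, and becomes less informative as the sample shrinks.

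The weakness is greatest in two places. One is the shortfall scenario, which the authors regard as the main risk and where the narrative comparison is the stated fallback. The other is confidence, one of the two outcomes in the policy example: the only survey tests specified for it by method are a baseline comparison and separate pre/post tests. At stake is whether the report can say anything quantitative about differential response, which bears on adapting the training to different audiences.

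**Working it through.** **Inputs from the protocol article (Quantitative pre- and post- survey).** Effect size d = 0.3, power 80%, two-sided alpha 0.05, 176 per group. **Assumed for illustration:** shortfalls to 100 or 60 per group; gains of 0.25 and 0.8 SD of the change score; equal SDs in the two groups; independent observations.

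**1. The plan's own figure.** Noncentral t with df = 2n − 2 and noncentrality d·√(n/2). At n = 175 per group power is 79.9%; at n = 176 it is 80.1%. The minimum of 352 (176 per group) is reproduced. It is a sample size for detecting a difference.

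**2. How often a real 0.3 SD gap is missed.** One minus the power from step 1:

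| Per group | Power | Missed |
|---|---|---|
| 176 | 80.1% | 20% |
| 100 | 56.0% | 44% |
| 60 | 37.1% | 63% |

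These rows shrink both groups. If only one group falls short and the other stays at 176, the gap is missed 33% of the time with 100 in the smaller group and 48% with 60.

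**3. What a non-significant difference leaves open.** The unadjusted 95% half-width is 1.96·√(2/n): at 176, 1.96·√(2/176) = 0.21 SD; at 100, 1.96·√(2/100) = 0.28 SD. An observed difference just short of significance at 176 per group (about 0.21 SD) has an upper limit near 0.21 + 0.21 = 0.42 SD.

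**4. What two significant within-group tests leave open.** Paired t power, noncentrality dz·√n, df = n − 1:

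| Pairs | Gain 0.25 SD | Gain 0.8 SD |
|---|---|---|
| 176 | 91% | about 100% |
| 100 | 70% | about 100% |
| 60 | 48% | above 99% |

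With 176 pairs per group, gains of 0.25 and 0.8 SD are both significant about 0.91 × 1.00 = 91% of the time, although one is more than three times the other (0.8/0.25 = 3.2).

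**5. The same example analysed as a difference in gain.** The difference is 0.8 − 0.25 = 0.55 SD. At 176 per group the expected 95% interval is about 0.55 ± 0.21, or 0.34 to 0.76. At 100 per group it is about 0.55 ± 0.28, or 0.27 to 0.83. In both cases the interval shows plainly what the two p-values conceal, from the same data.

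**The case against.** The strongest reply is that the policy sentence concerns an increase in each group, not an equal increase. Paired tests in both groups address that for the two groups studied, within the limits of an uncontrolled before-after design. Two unequal but positive gains would satisfy the sentence. It is also a conditional example in the Discussion, followed by an alternative, and not a planned hypothesis. This stands. A reader might infer that the plan has no analysis able to support the sentence; the document does not bear that out.

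Three other inferences are tempting and also fail:

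- **That the plan claims equal effects.** The phrase "ensure that all trainees are equipped equally to deliver MECC conversations" describes the goal of adapting the training later, and its sentence presumes that the training works differently for different audiences.
- **That a null group difference would be counted as success.** No passage says so; the plan says low power would be acknowledged.
- **That the claim becomes easier to reach as the sample shrinks.** On the literal reading the reverse holds: power for a 0.25 SD gain falls from 91% at 176 pairs to 48% at 60.

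Nor does the Discussion say that VCSE respondents in particular will be short.

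It is also fair that the baseline-adjusted regression could reveal unequal competence results. That does not help confidence, which is absent from its outcome list, and it does not rescue the narrative fallback. The regression is called logistic although competence is a mean score; that is a separate matter.

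**Conclusion.** The concern holds in a limited form. The stated fallback of narratively comparing two within-group results cannot show whether gains differ or are similar, and the specified between-group regression omits confidence, for which the study was sized. At the planned minimum of 176 per group, a true 0.3 SD gap goes undetected 20% of the time, and 44% at 100 per group. A 0.25 SD gain is significant 91% of the time with 176 pairs, so significance in both groups says little about relative size. The shortfall sizes and gains are illustrative assumptions, as are equal SDs and independent observations.

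This is an inexpensive improvement to the analysis and reporting. The policy example does not contradict the plan, provided it is read as an increase in the two groups sampled.

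**What to change.** - **Quantitative pre- and post- survey, and the shortfall text in the Discussion.** Replace the narrative comparison with an estimated between-group difference in pre-post gain, or in baseline-adjusted post score, with a 95% confidence interval. Report it for confidence and for each competence score (open discovery questions and SMARTER goal setting), whatever sample size is reached. The within-group tests can stay as descriptions of change.
- **Discussion, policy example.** Limit the statement to an increase in the two groups studied. Add that similarity will not be inferred from a non-significant group difference or from two significant within-group tests.

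**Cost.** One extra estimate per outcome and a few sentences, using survey data already being collected. The interval will be wide if recruitment is short (about ±0.28 SD at 100 per group), but it then shows openly how little is known.

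**Optional.** A formal equivalence margin is not required. If one is wanted it needs its own justification. The 0.3 in the sample size section is a detection target for post-training scores and should not simply be reused as a margin for gain. With an assumed margin of 0.3 SD and truly equal groups, equivalence would be shown about 76% of the time at 176 per group and 36% at 100.
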